### Triangulation of Mixed Methods Data

As part of the impact evaluation, one of the hypotheses being tested is “‘whether capacitated ANMs and MOs are able to translate their knowledge and skills to manage HRPs into practice.” This hypothesis will mainly be tested by triangulating both the datasets on the listed themes and indicators, particularly, during the end line (Table 5).

**Table 5. T5:** How qualitative and quantitative datasets will be triangulated and integrated?

Theme or indicator	System level data (qualitative)	Community level data (quantitative)
Training and handholding of ANMs^a^ and MOs^b^ on HRPs^c^	Early diagnosis of HRPs reported by ANMs or MOs Improved knowledge and skills to manage HRPs by ANMs and MOs Improved confidence to manage HRPs	Proportion of HRPs diagnosed in the first trimester Protocol-based management of HRPs Protocol-based referral of HRPs Proportion of unnecessary or irrational referrals
Motivation and satisfaction of ANMs and MOs	Digital tools facilitating improved counseling and follow-up of women with HRPs by ANMs and MOs	Proportion of mothers with HRPs counseled and followed up by ANMs and MOs Proportion of mothers with HRPs highly satisfied with management and referral practices of ANMs and MOs
Quality ANC^d^	Improvement in quality of ANC services reported by ANMs and MOs	Proportion of mothers whose weight, hemoglobin, and blood pressure were collected at least 4 times in pregnancy Proportion of mothers who received complete ANC package of services
Facilitators and barriers to HRP management	Specific nuances of facilitators and barriers to HRP management reported by system stakeholders	Proportion of mothers with HRPs using public health facilities for management Proportion of mothers using public health facilities for ANC, delivery, and PNC^e^ care

a ANM: auxiliary nurse midwife.

b MO: medical officer.

c HRP: high-risk pregnancy.

d ANC: antenatal care.

e PNC: postnatal care.

To operationalize triangulation as a methodological practice, the study will use structured integration matrices, defined timelines, and clearly delineated roles. The process will take place during the end line analysis phase (March-June 2026), once both qualitative and quantitative datasets have been collected and validated.

An integration matrix (Table 5) has been developed to align qualitative themes (eg, training, handholding, barriers, and motivation) with corresponding quantitative indicators (eg, timely diagnosis, referral patterns, and satisfaction with care). Systematic side-by-side mapping of these themes will facilitate the comparison of convergence, complementarity, and divergence between system-level perspectives of HWs and community-level experiences of pregnant women.

The qualitative team will conduct thematic analysis, while the quantitative team will undertake statistical analyses, including regression and DiD. A joint synthesis committee comprising senior researchers, program investigators, and biostatisticians will meet regularly during the end line analysis phase to review the matrices, address discrepancies, and ensure methodological rigor.

The integrated findings will be presented as narratives and summary tables, clearly highlighting areas where the 2 data streams converge or diverge. This structured approach enhances transparency, strengthens the validity of results, and ensures that triangulation moves beyond the conceptual intent to systematically document the facilitators and barriers to translating the knowledge gained from the program into practice on the ground by the HWs.

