The following literature provides quantitative evidence on the extent of gaps in correct management and referrals to HRPs at different levels of the public health care system in low- and middle-income countries, including India. A systematic review in India reported that due to the inability of PHCs to provide basic HRP care, the proportion of unjustified referrals to higher-level facilities ranged between 25%‐52% [18]. A study from Himachal Pradesh and Andhra Pradesh (AP) in India highlighted systemic gaps among health workers (HWs) across 3 tiers of the public health care system, as only 31% (47/147) of HWs from 3 tiers of the public health care system reported screening only for 10 out of 16 most common HRP conditions. Even among the 10 HRPs screened, only 35% (17/49) of HWs at PHCs and 51% (18/35) at CHCs reported managing identified HRPs at their facilities, while the remainder referred such cases. To specifically assess HRP management competencies, scenario-based assessments were conducted; “a second-trimester moderate anemia case scenario was given to HWs at 3 tiers of health care system in 2 states.” While nearly all HWs correctly diagnosed the condition and over 75% prescribed oral iron, only 5%‐45% prescribed iron injection, negligible prescribed tablet Mebendazole, and <10% provided nutritional counseling. Around 50% of HWs across tiers referred the case, although PHCs and CHCs are supposed to manage moderate anemia cases. Similarly, when a third-trimester pregnancy-induced hypertension (PIH) case scenario was given, all HWs made correct diagnosis. However, appropriate treatment varied, with 42% of PHCs and 71% of CHCs prescribing antihypertensive drug (MgSO_4_). Additionally, 94% at HSCs, 85% at PHCs, and 45% at CHCs reported referring such cases, although CHCs are supposed to manage PIH and preeclampsia cases. Thus, this study concluded that most referrals were very early and unnecessary, and few delayed referrals were coupled with poor prereferral management [15]. On preeclampsia and eclampsia diagnosis and management in 6 African countries, knowledge of diagnosis was excellent (>80%) in HWs, while knowledge on correct management varied (33%‐77%) and management in the event of convulsions was ≤51% [19]. A situational assessment study conducted in Telangana, India (2021‐2022) found that ANMs mainly manage anemia, and 94% of them refer all high-risk cases to specialists, thereby bypassing the established referral chain. The MOs and specialists also felt the need for training support in managing HRPs, as 25% of MOs lack clarity and confidence in handling HRPs, and only 60%‐65% of specialists possessed the requisite knowledge [20]. An important reason for suboptimal knowledge, lack of confidence, and confusion in role clarity in HRP management and referral across the 3 tiers of the health care system is the absence of standardized management and referral protocols for HRPs tailored according to these 3 tiers of health care system in India and other low- and middle-income countries.

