#### Hypothesis and Outcomes

The program’s impact evaluation will test the following research hypotheses: (1) Does the program, implemented over 18 months, enhance knowledge, skills, and confidence of the ANMs and the MOs to make early diagnosis and manage the 3 HRPs in the intervention arm, compared to usual care arm? (2) Can the capacitated ANMs and MOs translate their knowledge and skills into practice, particularly for early diagnosis and end-to-end management of the 3 HRP conditions in the intervention arm, compared to the control arm? (3) Does the program improve the quality of ANC services in the intervention arm, compared to the usual care arm?

At the system level, the primary outcomes focus on changes in the knowledge and skills of HWs. The first outcome is the net change in correct knowledge and skills of ANMs to manage (treat, counsel, refer, and follow-up) women with any of the 3 HRP conditions (anemia, PIH, and APH) from baseline to end line, comparing intervention and control arms. The second outcome is the net change in correct knowledge and skills of MOs to manage (treat, counsel, refer, and follow-up) women with any of the 3 HRP conditions (anemia, PIH, and APH) from baseline to end line, comparing intervention and control arms. The percentage of correct knowledge and skills for ANMs and MOs will be calculated based on the number of correct responses provided out of a total of 45 questions on the 3 HRPs, administered at baseline and end line surveys.

The system-level secondary outcomes include the net change in the ability of ANMs to correctly identify HRP-related signs and symptoms from baseline to end line, in intervention versus control arm and net change in the ability of MOs to do the same. Other outcomes include changes in the confidence level of ANMs and MOs to manage HRPs between baseline and end line across 2 arms and to document qualitatively whether any systematic barriers reported by district officials at baseline survey were overcome by the end line, by comparing intervention and control arms.

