At the community level, the primary outcome includes net change in the proportion of RDW with any of the 3 HRP conditions (anemia, PIH, and APH) whose problem was resolved prior to delivery and who reported satisfaction with the management of the condition, from baseline to end line, in intervention versus control arm. Satisfaction level of RDW is measured using a 5-point Likert scale on the topics of “attitude and behavior of staff,” “cleanliness and hygiene,” “comfort and care,” and “overall satisfaction with management of HRP condition at the facility.”

The community-level secondary outcomes include net change in proportion of RDW who received the complete ANC package during their last pregnancy*,* from baseline to end line, in intervention versus control arm. Also includes the net change in proportion of RDW who were sensitized about HRPs by ANM or MO during their last pregnancy*,* during baseline and end line, in intervention versus control arm. Other secondary outcomes include net change in the mean gestational month of first diagnosis of 3 HRPs by an ANM*,* from baseline to end line, in intervention versus control arm, and net change in the proportion of RDW diagnosed with any of the 3 HRPs who received protocol-based management or referral from an ANM*,* from baseline to end line, in intervention versus control arm. We also measure the net change in proportion of RDW diagnosed with any of the 3 HRPs, received protocol-based management or referral from MO*,* from baseline to end line in intervention versus control arm.

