### Sample Size of the Quantitative Surveys

The sample size of RDW to be included in the baseline and end line surveys was determined to generate indicators for each of the 3 HRP conditions (moderate or severe anemia, PIH, and APH) separately for the intervention and usual care arms. To achieve this, the sample size was estimated based on the HRP condition, with the lowest prevalence among the 3 conditions. This approach ensures that the sample size estimated for an HRP condition with the lowest prevalence will suffice for the HRP conditions with higher prevalence as well, using the most recent prevalence data for the HRP conditions among the pregnant women in India or North India.

From recent available literature in India, the prevalence of moderate or severe anemia among pregnant women in the north zone was 25% [39], PIH in India ranged from 5%‐17% [40], and prevalence of only APH is 2%‐5%, and placenta previa is 4%‐5% [41]. It implies, among the 3 HRP conditions, PIH has the lowest prevalence. Assuming the prevalence of PIH among RDW in the intervention arm and in the control arm, at baseline and end line surveys is 5%, the estimated sample size for PIH is not expected to differ by more or less than 1% (ie, 4%‐6% is the margin of error), with a 95% confidence level, the sample size of RDW required in both the intervention and in usual care arms, at baseline and at end line surveys is 1825 (rounded to 2000) [42]. It means we need to interview 2000 RDW in each arm, both at baseline and end line surveys to generate required sample size for each HRP condition. Assuming the above prevalence of HRPs holds true in the 2 study arms, by interviewing 2000 RDW cross-sectionally in each arm, we anticipate at least 400‐500 RDW with moderate or severe anemia, 120‐200 RDW with APH, placenta previa, or abruptio placenta, and 100‐340 women with PIH. Some of these RDW may have more than 1 of the 3 HRP conditions. Approximately 900‐1000 RDW in each arm will be without any of the 3 HRP conditions.

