Given the low prevalence of PIH and APH (around 5%), with 1% margin of error, our study (2000 RDW per arm) is adequately powered at 95% (a conservative estimate). With a higher margin of error (say 1.5%), although the required sample size per arm will reduce to 821, the power of the study will fall below 95%, and the anticipated number of RDW with PIH and APH would be too small to compare (approximately 70‐130 per arm). This would result in high CIs, making HRP-specific impact evaluation a challenging task.

As different respondents will be surveyed at baseline and end line, there is no risk of data attrition. However, since HRP conditions data in this study is relying on self-reports by RDW and expected low prevalence of PIH and APH conditions (around 5%) in India, nonparticipation by RDW with these conditions could compromise the statistical power of the study. To overcome this problem, we have set a narrow margin of error (1%, ie, prevalence could range between 4%‐6%) for baseline and end line estimates in each arm. Our sample size calculation also accounts for a 10% nonresponse rate per arm at both baseline and end line. To increase the effective prevalence of the APH condition, the inclusion criteria for this condition encompass APH, placenta previa, and abruptio placenta. With recent estimates in India showing an increase in prevalence of PIH to 11% [43], while moderate or severe anemia was stagnant at around 26% [39], we are confident of including sufficient RDW with these 2 conditions. Nevertheless, if the prevalence of any of the 3 HRPs falls below 4% at baseline or end line in either arm, the statistical power of the study for that HRP condition will be compromised. We acknowledge this as a limitation of the study.

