We will use the DiD technique to estimate the causal effect of program interventions on outputs (eg, RDW sensitized and HRPs diagnosed early) and outcomes (eg, protocol-based management and referral of HRPs). This approach compares changes in outputs and outcomes over the intervention period (18 months) between the intervention and the usual care arms. For each quantitative output and outcome indicator summary, descriptive DiD or net change will provide causal effect of intervention on the indicator. The DiD-specific regression models will then be used to test whether interventions were significantly associated with changes in the outcomes and to assess the extent of changes relative to the control group.

To address the issue of missing data in the RDW dataset, before applying DiD, we will assess the extent and patterns of missingness—whether missing data are at baseline, end line, or both—and examine whether missingness is random or systematically related to intervention status or outcomes by comparing covariates and outcomes between complete and missing cases. Given the robust data quality assurance measures implemented during both surveys, we anticipate minimal missingness, and any missing data are expected to be missing at random. If the proportion of missing at random for any outcome or covariate exceeds 10%, we will apply appropriate imputation methods prior to fitting the DiD model. The DiD model will then include intervention and control status, baseline and end line survey indicators, and interaction terms between outcomes and covariates.

During the granular analysis of testing the association between background characteristics and output and outcome indicators, we will draw upon the WHO’s Social Determinants of Health framework [45]. Intersectionality between the background and confounding variables will be explored using subgroup analysis. In the multivariate regression model, predictor variables will only be included after testing for multicollinearity using variance inflation factor to ensure stability and reliability of the model.

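### Table 5's first-trimester measure of early diagnosis can in effect score only anemia, and the mean month of diagnosis, if pooled over three conditions, moves with case mix

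*Protocol article*

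**What the plan says.** The second hypothesis asks whether trained auxiliary nurse midwives (ANMs) and medical officers put their skills into practice, "particularly for early diagnosis and end-to-end management of the 3 HRP conditions in the intervention arm" (Hypothesis and Outcomes). The section on triangulation makes the side-by-side comparison in Table 5 the main test of that hypothesis. In its first row the qualitative item is "Early diagnosis of HRPs reported by ANMs or MOs", and the only quantitative item on timing of diagnosis is "Proportion of HRPs diagnosed in the first trimester". No condition is named and no cutoff by condition is given.

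A community-level secondary outcome also concerns timing: "net change in the mean gestational month of first diagnosis of 3 HRPs by an ANM" (Hypothesis and Outcomes). Data Analysis then lists early diagnosis among the indicators whose causal effect is to be estimated by difference-in-difference (DiD): "outputs (eg, RDW sensitized and HRPs diagnosed early".

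Other passages point toward analysis by condition. The surveys are sized to "generate indicators for each of the 3 HRP conditions (moderate or severe anemia, PIH, and APH) separately" (Sample Size of the Quantitative Surveys), and a smaller sample is rejected partly as "making HRP-specific impact evaluation a challenging task". Table 3 records the timing of first diagnosis, and who made it, among the details collected for each condition.

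**The concern.** The three evaluated conditions do not become diagnosable at the same stage of pregnancy. Moderate or severe anemia can be found at a first visit. PIH and APH, as usually defined, belong to the later part of pregnancy. The article states no onset windows. Its nearest hint is a cited study in the Introduction, where the PIH vignette is set late: "when a third-trimester pregnancy-induced hypertension (PIH) case scenario was given".

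If that premise is accepted, a first-trimester cutoff applied to all conditions counts every PIH and APH case as not early, however promptly it was found. A single mean month over the three conditions has a related weakness: it depends on which conditions were diagnosed as well as on how soon each was found. The program aims to improve identification, so the mix of diagnosed conditions may well change in the intervention arm. At stake is whether the early-diagnosis part of the second hypothesis is judged on figures that track timeliness.

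**Working it through.** **The plan's own figures.** The survey size is a single-proportion precision calculation: 1.96² × 0.05 × 0.95 / 0.01² = 1824.7, so 1825, rounded up to 2000 per arm per survey. It concerns prevalence; no size is derived for either timing indicator. The expected cases per arm follow from 2000 women:

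- Anemia: 25% gives 500; the article states 400 to 500.
- APH group: 2% + 4% = 6% gives 120, and 5% + 5% = 10% gives 200.
- PIH: 5% gives 100, and 17% gives 340. The 11% cited as a recent estimate gives 220.

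**Ceiling of the first-trimester proportion.** Assume that no PIH or APH case can be a first-trimester diagnosis, that the denominator is these three conditions, and that no woman has two of them. The highest attainable value is anemia / (anemia + APH + PIH).

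- Lowest: 400 / (400 + 200 + 340) = 400/940 = 42.6%.
- Highest: 500 / (500 + 120 + 100) = 500/720 = 69.4%.

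So 31% to 57% of cases cannot score.

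**Effect of finding more PIH on that proportion.** Take 500 anemia, 160 APH and 100 PIH cases, and assume that 20% of anemia is found in the first trimester throughout.

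- PIH 100: 100/760 = 13.2%.
- PIH 220: 100/880 = 11.4%.
- PIH 340: 100/1000 = 10.0%.

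Timeliness is unchanged, yet the indicator falls.

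**Mean month, if pooled.** Assume mean diagnosis at month 4 to 6 for anemia and month 7 to 8 for PIH and APH; the article gives no such means. Keep 500 anemia and 160 APH cases in the intervention arm and raise PIH there. Control is held unchanged. The share of later-onset cases goes from 260/760 = 34.2% to 380/880 = 43.2% (PIH 220) or 500/1000 = 50.0% (PIH 340). The case-mix shift in the pooled mean is

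shift = (gap between later-onset mean and anemia mean) × (change in later-onset share),

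that is, gap × 0.0897 or gap × 0.1579. With a true gain of 0.25 month in every condition, the net change is shift − 0.25 (negative means earlier):

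| Gap (months) | PIH to 220 | PIH to 340 |
|---|---|---|
| 1 | -0.16 | -0.09 |
| 2 | -0.07 | +0.07 |
| 3 | +0.02 | +0.22 |
| 4 | +0.11 | +0.38 |

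The gain is understated in every cell. The sign reverses only when the gap exceeds 0.25/0.0897 = 2.8 months (PIH 220) or 0.25/0.1579 = 1.6 months (PIH 340).

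**Role of the control arm.** If control has the same rise in PIH and the same condition means at baseline, its mean moves by the same shift and the DiD returns −0.25. The distortion comes only from the excess rise in the intervention arm.

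**By condition.** Each condition's mean moves by −0.25, whatever happens to the mix between conditions.

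**The case against.** The strongest reply is that pooling of the mean is inferred. Neighboring outcomes speak of any of the three conditions, which is clearly pooled wording, while the timing outcome does not. The sample-size section aims at indicators for each condition, and timing is collected by condition. This stands in part: one mean over three conditions is the more natural reading, but the article does not say so.

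A reader might infer that finding more PIH or APH must show up as later diagnosis. The documents do not support that. A rise common to both arms cancels in the DiD, and a reversal depends on the size of the excess rise, the gap between conditions and the true gain. For example, take 450 anemia and 120 APH cases, PIH going from 100 to 200, and means of month 5 and month 8. A gain of 0.3 month in every condition moves the mean from (450×5 + 220×8)/670 = 5.99 to (450×4.7 + 320×7.7)/770 = 5.95. The gain almost disappears, but the sign is right.

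The inputs are also imperfect. Table 5 refers to HRPs generally, and the survey records other conditions too, so the ceiling depends on the denominator assumed. The expected counts cover all women with a condition, whereas the mean covers diagnoses by an ANM, whose mix may contain more anemia. A ceiling by itself weakens an effect and does not reverse it.

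None of this rescues the Table 5 indicator, which is explicit and has no cutoff by condition. Nor is this a detail that can be left to an analysis plan: the objection is to what the stated indicator measures.

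**Conclusion.** The point holds firmly for Table 5 and conditionally for the mean month.

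For Table 5, given that PIH and APH are not first-trimester diagnoses, the indicator reflects essentially anemia alone. It cannot exceed about 43% to 69% on the expected counts, and it falls as more PIH or APH is found. The range assumes a three-condition denominator and no overlap. The onset premise rests on the usual definitions of the conditions and not on the article; a vignette set in the third trimester does not establish the diagnosable window.

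For the mean month, if it is pooled and PIH or APH detection rises more in the intervention arm, a true 0.25-month gain in every condition appears as -0.16 to +0.11 month with PIH at 220, and -0.09 to +0.38 with PIH at 340. These figures rest on the assumed condition means and on an unchanged control arm.

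One triangulation indicator and one secondary outcome are affected. No primary outcome is touched, and the second hypothesis also rests on indicators of management and referral. The correction is worth making before the end line analysis, because early diagnosis is named in that hypothesis.

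**What to change.** - In Table 5, restrict the first-trimester proportion to moderate or severe anemia.
- In Hypothesis and Outcomes, state the mean gestational month of first diagnosis by an ANM separately for anemia, PIH and APH, each with its own DiD. A woman with two conditions then contributes to each.
- Base the early-diagnosis conclusion for the second hypothesis on these results and not on a mean over conditions.

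This matches the sample-size section's stated aim and needs no new data, since timing and diagnosing cadre are already collected by condition. The cost is two more rows of analysis and wider intervals for PIH and APH. At equal standard deviation, and ignoring clustering, the standard error on 100 PIH cases is √(760/100) = 2.8 times that on 760 pooled cases; for 160 APH cases it is √(760/160) = 2.2 times. The split removes the mixing between conditions only. If the additional cases within one condition arise later than those found before, that condition's mean will still move, and the report should say so.
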